#### Instruments

2.3.2.

##### Social and emotional skills

2.3.2.1.

Social and emotional skills will be assessed using two instruments.

Four subscales (with eight items each) of the Organization for Economic Co-operation and Development (OECD) Study on Social and Emotional Skills (SSES; Organisation for Economic Co-operation and Development, 2021) will be used to evaluate self-control (e.g., “I stop to think before acting”), cooperation (e.g., “I am always willing to help classmates”), empathy (e.g., “I understand what others want”), and stress resistance (e.g., “I am relaxed and handle stress well”). The items are answered on a 5-point Likert-type scale from 1 (completely disagree) to 5 (completely agree). The Portuguese version that will be used presents satisfactory levels of internal consistency (ranging from *α* = 0.67 to *α* = 0.74 for the subscales that will be used; Organisation for Economic Co-operation and Development, 2021).

Two subscales of Difficulties in Emotion Regulation Scale (DERS; Gratz and Roemer, 2004) will be used to assess two components of emotion regulation, specifically “limited access to emotion regulation strategies” (eight items; e.g., “When I’m upset, it takes me a long time to feel better”) and “lack of emotional clarity” (five items; e.g., “I am confused about how I feel”). These items are answered on a 5-point Likert-type scale from 1 (“almost never applies to me”) to 5 (“almost always applies to me”). The higher the score on each of the subscales, the greater the participants’ emotion regulation difficulties. The Portuguese version that will be used presents good internal consistency (*α* = 0.88 and *α* = 0.75, respectively) for these two subscales (Coutinho et al., 2010).

##### Well-being

2.3.2.2.

The EPOCH Measure of Adolescent Well-Being (Kern et al., 2016) will be applied to evaluate five positive psychological characteristics considered to contribute to well-being, physical health, and other positive outcomes: engagement (e.g., “I get completely absorbed in what I am doing”), perseverance (e.g., “I finish whatever I begin”), optimism (e.g., “I am optimistic about my future”), connectedness (e.g., “When I have a problem, I have someone who will be there for me”) and happiness (e.g., “I feel happy”). Each subscale is composed of four items, answered on a 5-point Likert-type scale from 1 (almost never/not at all like me) to 5 (almost always/very much like me). Both the original and the Portuguese version that will be used (Francisco et al., 2019a) present good internal consistency (from *α* = 0.74 to *α* = 0.86, and from *α* = 0.82 to *α* = 0.93, respectively).

##### Health literacy

2.3.2.3.

The Health Literacy for School-Aged Children (HLSAC; Paakkari et al., 2016) will be used to assess students’ subjective health literacy. It is composed of 10 items, two items from each of five predetermined theoretical components: theoretical knowledge (e.g., “I have good information about health”), practical knowledge (e.g., “When necessary, I find health-related information that is easy for me to understand”), critical thinking (e.g., “I can usually figure out if some health-related information is right or wrong”), self-awareness (e.g., “I can give reasons for choices I make regarding my health”), and citizenship (e.g., “I can judge how my own actions affect the surrounding natural environment”). The items have a 4-point Likert-type response scale from 1 (not at all true) to 4 (absolutely true). The sum of the answers allows the identification of the participants’ levels of health literacy: “low” (score 10–25), “moderate” (score 26–35), and “high” (score 36–40; Paakkari et al., 2018). Both the original (Paakkari et al., 2016) and the Portuguese version (Francisco, 2020) that will be used present good internal consistency for total score (*α* = 0.93 and *α* = 0.87, respectively).

Twelve items from the young people version of the Mental Health Literacy Questionnaire (MHLq; Campos et al., 2016), directly related to the contents on mental health literacy covered by #EntreViagenseAprendizagens, were selected to serve as indicators of self-help strategies (four items; e.g., “Physical exercise helps to improve mental health”), first aid skills and help-seeking (four items; e.g., “If a friend of mine developed a mental disorder, I would encourage her/him to get medical support”), and knowledge/stereotypes (four items; e.g., “Mental disorders affect people’s thoughts”) about mental health. The items have a 5-point Likert-type response scale from 1 (strongly disagree) to 5 (strongly agree). The original version of this questionnaire, with 34 items, presents good internal consistency (from *α* = 0.72 to *α* = 0.79 for each factor, and *α* = 0.84 total score).

##### Health-related knowledge, attitudes, and behaviors

2.3.2.4.

To evaluate knowledge, attitudes, and behaviors associated with health, 14 items answered on a Likert-type scale from HBSC studies (Inchley et al., 2018) will be used. They relate to physical activity (e.g., “In the last 7 days, in how many days did you accumulate at least 60 min of physical activity (e.g., gymnastics, sports, playing football, walking to school, etc.)?”), alcohol and tobacco consumption (e.g., “How often do you smoke tobacco?”), screen time (“In your free time, during the week, how much time per day do you use screens such as iPads, television, cell phones, or computers?”), eating habits (e.g., “During the week how often do you eat soup?”), and sleep habits (e.g., “How many hours, on average, do you sleep at night on weekdays?”).

Five multiple-choice questions, adapted from the Questionnaire of Nutrition (NUT-Q; Raich et al., 2008), will be also used to measure knowledge of nutrition and particular types of food. For example: “Which of the following nutrients constitute the body’s main energy reserve?” (possible answers: proteins; vitamins and minerals; fats; carbohydrates; I do not know). The sum of the correct answers corresponds to the total value for this dimension (ranging from 0 to 5).

Four items, taken from the Portuguese barometer for physical activity (Silva et al., 2018), will be used to assess students’ knowledge about physical activity. Participants indicate on a 5-point Likert-type scale their level of agreement with the sentences presented (e.g., “Climbing stairs or walking is not physical activity,” “Only high-intensity physical activity has beneficial effects”).

##### Relationships with others

2.3.2.5.

Specific items from HBSC studies (Inchley et al., 2018) will be used to evaluate students’ peer acceptance (e.g., “My classmates accept me for who I am”) with a Likert-type scale from 1 (“False most of the times”) to 3 (“True most of the times”), as well as their participation in situations of conflict or violence (e.g., “How many times have you taken part in provocations to another student(s), in the last 2 months?”), with a five Likert-type scale from 1 (“I did not take part in provocations”) to 5 (“Several times a week”).

Two items to assess the students’ relationship with both parents will be also presented (e.g., “How do you evaluate your relationship with your mother?”), answered on a 5-point Likert-type scale from 1 (“Very bad”) to 5 (“Very good”).

##### Sociodemographic data

2.3.2.6.

Information about the sociodemographic characteristics of students and their parents will be collected for the present study, including sex, age, special educational needs, household, and parents’ marital status and level of education, among others.

#### Data analysis

2.3.3

Descriptive statistics will be used to describe intervention and control group participants, replying to the pre-test, post-test, and follow-up questionnaires. To assess intervention effectiveness, statistically significant differences (and effect sizes) between the intervention and control groups will be examined by repeated measures ANOVA, contrasting results from the intervention and control groups (between-subjects factor) on the different outcome measures (e.g., social and emotional skills, health literacy, well-being) at pre-test, post-test, and follow-up (within-subjects factor).

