#### Structure of sessions with students

2.2.3.

The sessions are implemented with groups of 12–15 students, with one facilitator per group. All sessions have clearly defined learning goals, and are dynamic and interactive, with a duration of 50 min (i.e., the same duration as regular curricular classes, in order to maximize the adolescents’ attention and encourage adoption of the program by creating the possibility of integrating it into regular curricular units). Most sessions are structured as follows: a semi-structured individual (or group) activity, a semi-structured activity in small groups, and a final interactive debate on what was learned during the session.

Although there are always one or two key skills that are the focus of each session, in the same session several competencies can be worked on, given their association with different themes and the use of different types of activities. For example, in session #14, titled “Parliament,” the main theme is communication (focusing on assertive communication as an important social and emotional skill); however, the themes covered in the scenarios presented to the students for the role-play concern different issues, such as (un)healthy behaviors, making it possible to work on health literacy at the same time.

At the end of each session, a “healthy tip” associated with the topic that was addressed during that session (e.g., #gratitude) is discussed and complemented with a “challenge of the week.” This challenge is an intersession activity to be developed during the week (e.g., “gratitude agenda”) and related to the content of the session. This activity can be shared and discussed at the next session if the participants so wish.

In the first session, each student will receive a folder in which to place all the activity sheets completed during the program. This folder will then serve as a portfolio and a record of the student’s evolution and involvement.

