#### Design and procedure

2.3.1.

A cluster randomized controlled trial design will be used for impact evaluation, with 8th grade classes (units of randomization) from three public schools being assigned to either the intervention or the control condition. Data collection will be based on structured questionnaires applied to all students, both in the control group and the intervention group. Baseline measures (T0) will be collected with all potential participants prior to intervention implementation. In each school, three classes will then be randomly selected to be part of the intervention group in Year 1, while the remaining classes will be the control group. Students who integrate the control group in Year 1 will be part of the Intervention Group in Year 2. The post-test (T1) will take place approximately 1 week after the end of the program and the follow-up (T2) will take place 9 months later.

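### Whole classes are randomised, but effectiveness is tested with a repeated measures ANOVA on arm and time only, which leaves out the unit of randomisation and raises the type I error by an amount that depends on an unstated class-level correlation

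*Protocol article*

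**What the plan says.** Section 2.3.1 (Design and procedure) is explicit about the design: "A cluster randomized controlled trial design will be used for impact evaluation, with 8th grade classes (units of randomization"). Allocation is within school: "In each school, three classes will then be randomly selected to be part of the intervention group in Year 1". All classes not drawn serve as controls. With three schools, that makes nine intervention classes and an unstated number of control classes.

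Section 2.3.3 (Data analysis) fixes the effectiveness test. Differences "between the intervention and control groups will be examined by repeated measures ANOVA, contrasting results from the intervention and control groups (between-subjects factor") are assessed on each outcome "at pre-test, post-test, and follow-up (within-subjects factor"). Arm and time are the only factors named. The article mentions no class or school term, random effect, multilevel model, cluster-robust error, ICC or design effect.

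Section 2.2.3 (Structure of sessions with students) adds a second layer of grouping in the intervention arm: "The sessions are implemented with groups of 12–15 students, with one facilitator per group".

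**The concern.** In a repeated measures ANOVA with arm between subjects and time within subjects, the error terms come from variation between and within students. The design allocates classes. Students in a class share peers, teachers and a timetable, and those in the programme also share group sessions and a facilitator. If their scores, or their changes in score, are correlated for these reasons, the difference between arms varies more than the student-level error term allows.

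This is the only effectiveness test described, and it serves all seven hypotheses in section 2.2.2. If it is anti-conservative, the programme could be declared effective on some outcomes because a few classes happened to move together. The article also plans publication, a technical manual and facilitator training (section 3), so the error rate matters beyond this trial.

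**Working it through.** **Inputs from the article.** Unit of randomisation: class. Intervention classes: 3 per school x 3 schools = 9. Waves: T0, T1, T2. There is no stated sample size, alpha or ICC, so there is no figure of the plan's own to reproduce.

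**Assumptions.** Two-sided 5% test; 9 control classes (3 per school); m = 20-25 analysed students per class; ICC of change (rho) from 0.01 to 0.10.

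**Step 1: degrees of freedom.** Under these assumptions there are 18 classes. A class-level comparison adjusted for three schools has 18 - 3 - 1 = 14 error degrees of freedom. The student-level between-subjects error has 18 x 20 - 2 = 358 to 18 x 25 - 2 = 448.

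**Step 2: true error of a nominal 5% pre-post test.** Design effect DE = 1 + (m - 1) x rho. True error = 2 x [1 - Phi(1.96 / sqrt(DE))]. Example: m = 20, rho = 0.02 gives DE = 1 + 19 x 0.02 = 1.38; 1.96 / sqrt(1.38) = 1.67; error 9.5%.

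| rho | DE, m=20 | Error, m=20 | DE, m=25 | Error, m=25 | Simulated, 9 vs 9 classes (m=20; m=25) |
|---|---|---|---|---|---|
| 0.01 | 1.19 | 7.2% | 1.24 | 7.8% | 7.2%; 8.0% |
| 0.02 | 1.38 | 9.5% | 1.48 | 10.7% | 9.0%; 11.7% |
| 0.05 | 1.95 | 16.0% | 2.20 | 18.6% | 15.9%; 18.9% |
| 0.10 | 2.90 | 25.0% | 3.40 | 28.8% | 24.9%; 28.2% |

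Formula and simulation agree. Over a wider range (m = 12 to 28, rho = 0.005 to 0.10) the formula gives 5.6% to 30.8%.

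**Step 3: which ANOVA term is tested.** The three-wave student-level ANOVA was simulated under no effect (3,000 runs per scenario, m = 20, 3 + 3 classes in each of 3 schools). Variance left after the class components was split equally between stable student differences and residual.

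| Stable class variance share | Class-by-time share | Group main effect | Group-by-time |
|---|---|---|---|
| 0.05 | 0 | 19.6% | 4.9% |
| 0.01 | 0.01 | 9.2% | 11.1% |
| 0.02 | 0.02 | 14.3% | 17.8% |
| 0.05 | 0.05 | 25.1% | 36.8% |

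The first row is the important one. Class differences that do not change over time inflate the main effect but leave the group-by-time test at its nominal level. The interaction is inflated only when classes change differently from one another.

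**Step 4: putting the two tables on one scale.** A class-by-time share of total variance is not an ICC of change. In the second row of step 3 the residual is (1 - 0.01 - 0.01) / 2 = 0.49, so rho = 0.01 / (0.01 + 0.49) = 0.02. The matching pre-post figure is therefore 9.5%, against 11.1% for the two-degree-of-freedom interaction. In the last row the residual is (1 - 0.05 - 0.05) / 2 = 0.45 and rho = 0.05 / 0.50 = 0.10: 25.0% against 36.8%.

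**Step 5: sensitivity to the number of controls.** With shares of 0.02 each, 2 or 5 control classes per school give 16.7% and 17.3% for group-by-time, against 17.8% with 3. The unstated number of control classes hardly matters for this point.

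**Step 6: does a class-level analysis repair it?** An analysis of class mean change from T0 to T1, adjusted for school, rejected in 4.4-5.5% of runs in every scenario. The simulation standard error is sqrt(0.05 x 0.95 / 3000) = 0.4 percentage points, so this is nominal.

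**The case against.** A statistical analysis plan that is not shown might handle clustering. That defence is weak: the article does not leave the method open but names the test and its factors, and accounting for class would mean replacing that test.

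The objections to size are stronger, and they stand.

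- A reader might infer that false-positive rates are well above 5% whatever the ICC. The article gives no ICC or class size, so it does not support that. At an ICC of change of 0.01 the excess is two to three percentage points; a marked excess needs about 0.02 or more.
- A reader might infer that shared teachers, peers and timetable are enough to invalidate the group-by-time test. Where such differences are stable and already present at baseline, they cancel in that term. What inflates it is differential change between classes. Delivery in facilitated groups makes this plausible, but the article does not quantify it.
- A reader might conclude that the three-wave test is several times worse than the pre-post test. Much of that impression comes from comparing a share of total variance with an ICC of change. With a between-student share of 0.6, a class-by-time share of 1% is an ICC of change of about 0.01 / 0.40 = 0.025. On a common scale the interaction is still more inflated, but the gap is smaller.
- Randomisation within school means that school-level variance largely cancels between arms if allocation ratios are similar, so the relevant ICC is that of classes within schools.
- Section 2.3.3 plans significance tests and effect sizes and mentions no confidence intervals, so the documents cannot be faulted for intervals that are too narrow.

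**Conclusion.** The point holds as a mismatch between design and analysis: classes are randomised, and the named test has no class-level error term. The direction is certain for any positive class-level correlation in the tested contrast. The size is conditional. With 20-25 students per class, a nominal 5% pre-post test runs at about 7-8%, 9-12%, 16-19% and 25-29% for an ICC of change of 0.01, 0.02, 0.05 and 0.10. The group main effect is also exposed to stable class differences, and section 2.3.3 does not say which term decides effectiveness. This should be corrected before the data are analysed, because it affects every effectiveness result and costs little to put right.

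**What to change.** In section 2.3.3, replace the student-level repeated measures ANOVA with an analysis that respects class randomisation. Either of these is enough:

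- a linear mixed model with fixed group, time, group-by-time and school, random class and class-by-time effects, within-student correlation across waves, and Kenward-Roger or Satterthwaite degrees of freedom; or
- a class-level analysis of change adjusted for school.

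State that the group-by-time contrast is the test of effectiveness, and report effect sizes with cluster-adjusted confidence intervals and the observed ICC. A facilitator-group effect is at most a sensitivity analysis: with about nine intervention classes it may not be separable from class, and section 2.2.3 does not say how delivery groups map to classes or whether one facilitator leads several.

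The cost is a revised paragraph, slightly more modelling, wider intervals and fewer error degrees of freedom (14 rather than several hundred under the assumptions above). Design and data collection are unchanged, provided that class and school are recorded for each student.

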### Intervention

2.2.

#EntreViagenseAprendizagens is a 20-week school-based intervention that uses the metaphor of a journey to a better world, for which students must prepare through learnings and skills they put in their “luggage.” These learnings and skills are obtained by “making a stop” at different places in the city (e.g., “Market of Emotions,” “Mind Gym”), which correspond to the various sessions. This metaphor aims to illustrate the preventive and holistic nature of the intervention.

As recommended for effective SEL programs, the design of the program was based on the SAFE (acronym for Sequenced, Active, Focused, and Explicit) approach (Durlak et al., 2011). Indeed, #EntreViagenseAprendizagens adopts a sequential training approach (e.g., activities on emotion recognition precede activities on emotion regulation strategies), uses active forms of learning, based on experiential and participatory activities (e.g., role-playing, debates), devotes sufficient time to skill development, and has explicit learning goals. The development of skills is facilitated by experiential and participatory learning during the sessions, but their application in other contexts is also promoted, notably through challenges proposed to be carried out during the week (e.g., activities to be developed by the students together with their families).

Five characters were created within the scope of the program and will be used to accompany the students throughout the intervention (Figure 1). The characters are teenagers with diverse characteristics (e.g., characters with different ethnicities and weights, a character with impaired mobility). The aim is to make it easier for all the students to identify with the themes of the program and to enhance their engagement with the intervention. The characters are featured in the four videos designed specifically for this program, which focus on themes covered in the sessions (#HealthLiteracy, #MentalHealthLiteracy, #CharacterStrengths, #Communication) and in the activity sheets used during the program. An Instagram^®^ account for #EntreViagenseAprendizagens will be set up and used throughout the program to recall the “healthy tips” and run the “Well-being-Promoting Actions” photo contest (see below).

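### A single three-wave repeated measures ANOVA makes the post-test effect depend on answering the 9-month follow-up

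*Protocol article*

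**What the plan says.** The protocol article, section 2.3.3 (Data analysis), names one effectiveness analysis. Differences between arms "will be examined by repeated measures ANOVA, contrasting results from the intervention and control groups (between-subjects factor"), with outcomes taken "at pre-test, post-test, and follow-up (within-subjects factor"). All three waves are thus levels of one factor in one model. The section mentions no imputation, no likelihood-based model and no separate comparison of T0 with T1.

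The timing is in section 2.3.1 (Design and procedure): "Baseline measures (T0) will be collected with all potential participants prior to intervention implementation", and then "The post-test (T1) will take place approximately 1 week after the end of the program and the follow-up (T2) will take place 9 months later". Section 2.2 (Intervention) gives the programme length: "EntreViagenseAprendizagens is a 20-week school-based intervention". Section 2.2.6 limits the evaluation to 8th grade students.

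Two other statements bear on the point. Section 2.2.2 lists seven hypotheses about programme effects and adds maintenance at 9 months as a further one. Section 2.3.1 says that the Year 1 controls move into the intervention group in Year 2.

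**The concern.** Classical repeated measures ANOVA works on a complete set of outcomes per student. A student who answered T0 and T1 but not T2 is either imputed or dropped, and the article does not speak of imputing. If dropped, the student contributes nothing to the arm-by-time test or to its post-test contrast, although both values needed for that contrast were collected.

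The comparison affected is the cleanest one in the trial. T1 comes about a week after the programme ends, before the controls receive it, and answers the seven effect hypotheses without any use of T2. Under the named method it would be estimated only in students who also respond 9 months later, which is a selection made after randomisation. At stake are the precision of the T1 effect and, under some patterns of non-response, its validity.

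**Working it through.** The article gives no sample size, power, expected dropout or intraclass correlation (ICC), so there is no planned figure to reproduce. The timing below comes from the document. Every loss rate, class size and ICC is an assumption.

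**1. When T2 falls.** Programme 20 weeks (section 2.2), T1 about 1 week later and T2 9 months after that (section 2.3.1). Nine months is 9 × 52.18 / 12 = 39.1 weeks. T0 to T2 is at least 20 + 1 + 39.1 = 60.1 weeks. That exceeds one year, so students enrolled in 8th grade at T0 reach T2 in a later school year.

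**2. Whether the method needs all waves.** A standard repeated measures ANOVA routine, run with a within-subjects factor on simulated three-wave data with some T2 values missing, stopped with an error that the data were unbalanced. Incomplete students must be removed or filled in before such an analysis runs.

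**3. Precision, ignoring clustering.** If a fraction d of the students with T0 and T1 data lacks T2 at random, the standard error (SE) of the T1 effect is multiplied by 1/√(1 − d). An analysis with 80% power at full data (two-sided 5%) then has power Φ[(1.960 + 0.842)·√(1 − d) − 1.960].

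| Assumed T2 loss d | SE multiplier | Power (80% at full data) |
|---|---|---|
| 10% | 1.054 | 76% |
| 20% | 1.118 | 71% |
| 30% | 1.195 | 65% |

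**4. Precision with clustering.** Classes are randomised, and with a fixed number of classes the variance per class mean is proportional to [1 + (m − 1)·ICC]/m for m students. Assume m = 20, ICC = 0.05 and loss spread evenly over classes.

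- Full data: 1.95/20 = 0.0975.
- 10% loss, m = 18: 1.85/18 = 0.1028; SE multiplier √(0.1028/0.0975) = 1.03.
- 20% loss, m = 16: 1.75/16 = 0.1094; SE multiplier √(0.1094/0.0975) = 1.06.
- 30% loss, m = 14: 1.65/14 = 0.1179; SE multiplier √(0.1179/0.0975) = 1.10.

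The cost is about half that in step 3, because losing students within a class matters less than losing classes.

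**5. Bias.** Simulation with 360 students, outcome SD 1, correlations between waves 0.5 to 0.6, a true T1 effect of 0.25 SD, no clustering and 2,000 runs. The estimate is the arm difference in change from T0 to T1.

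| T2 loss pattern (nominal 10 / 20 / 30%) | All students with T0 and T1 | Three-wave completers |
|---|---|---|
| Random | 0.25 / 0.25 / 0.25 | 0.25 / 0.25 / 0.25 |
| Low T1 scorers in the intervention arm likelier to miss T2 | 0.25 / 0.25 / 0.25 | 0.28 / 0.31 / 0.33 |

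Random loss left about 324, 288 and 252 of the 360 students and caused no bias. The second row shows only what one chosen pattern would do; the document does not support that pattern over another.

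**The case against.** The strongest reply is that the article contains no exclusion rule. Listwise deletion is a property of the method, not a written decision. Analysis sets and missing-data handling are commonly left to a fuller plan, and imputation before the ANOVA, or a T0 to T1 analysis beside it, would be compatible with the text. This stands as far as it goes: a reader might infer that the plan states it will exclude incomplete students, and it does not. It does not remove the point, because the article does fix the method and describes no device that would avoid the consequence.

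Three stronger readings are tempting and unsupported.

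- A reader might take "replying to the pre-test, post-test, and follow-up questionnaires" as defining an analysis set of three-wave respondents. The phrase belongs to the sentence on descriptive statistics and says nothing about who enters the effectiveness test.
- A reader might infer bias from any difference between arms in T2 response. Loss that depends on arm alone is random within arm; it costs precision and leaves the T1 contrast unbiased.
- A reader might expect loss to be worse among controls because only the intervention arm has been engaged by the programme. That is true at T1. T2 falls in a later school year, and controls enter the programme in Year 2, so they may be receiving it, or have received it, by then.

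It is also fair to object that the document gives no rate or pattern of non-response. Loss through school moves, grade repetition or absence is a reasonable expectation over more than a year, but it is an expectation only.

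**Conclusion.** The point holds in a limited form. The named analysis, in its classical form, ties the post-test effect to a wave that this effect does not need and that comes at least 60 weeks after baseline.

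The certain consequence, given any T2 loss and no imputation, is reduced precision. It is modest with clustering (roughly 3 to 10% on the SE for 10 to 30% loss under the class size and ICC assumed above) and larger if clustering is negligible (5 to 20%).

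Bias is possible, not shown. It requires T2 non-response related to outcome, mainly with a relation that differs by arm. Its direction cannot be predicted from the document. The flaw does not invalidate the trial, but it is avoidable and should be corrected before the data are analysed.

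**What to change.** In section 2.3.3, replace the repeated measures ANOVA with a likelihood-based linear mixed model. Include every available wave from all students in the randomised classes, analysed in the arm to which their class was assigned. Fit class as a random effect, allow for correlation between a student's repeated measures, and report the arm contrast at T1 and at T2 separately. The T1 effect then does not depend on whether a student answers T2.

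The cost is a change of wording and slightly more analysis work, with no new data. The model assumes that missing values are missing at random given the observed ones. That is weaker than what the completers-only analysis needs, but it should be stated.
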